## Abstract

**Background:**

Increasing physical activity (PA) levels and reducing sedentary behaviors in children and adolescents is a need, especially in schools. Active breaks and physically active learning are examples of two emerging methodologies that have been shown to be effective in increasing PA levels and additionally produce improvements in children’s educational markers. However, the evidence in adolescents is very limited. This paper presents the design, measurements, and interventions implemented in the ACTIVE CLASS study, whose objectives are: (i) evaluate the effects of two interventions on PA levels, sedentary time, health-related physical fitness academic indicators, cognition, and markers of psychological health among secondary education students; (ii) evaluate teachers’ and students’ experiences about the implementation of these the two school-based PA intervention.

**Methods:**

A randomized controlled study is conducted with a total of 292 students aged 12–14 years old from six schools (7th and 8th grade) in Spain (three in Cadiz and three in Caceres). One school from each study provinces is randomly assigned to either the active break intervention group, the physically active learning intervention group, or the control group. The interventions have a duration of 16 weeks. Nine main measurement categories are assessed: PA and sedentary time, health-related physical fitness, academic indicators, cognition, psychological health, motivational variables, dietary patterns, sociodemographic characteristics, as well as qualitative information through semi-structured individual interviews and focus groups. Three independent measurements of evaluation are distinguished: pre-intervention, post-intervention (week 16) and retention measurement (4 weeks after the intervention). For quantitative variables, descriptive, correlational, regression and repeated measures ANOVA will be applied.

**Discussion:**

To the best of our knowledge, the ACTIVE CLASS study is the first of its kind in Spain to evaluate the effects of incorporating active breaks and physically active learning in secondary education. In addition, this project provides important information on the effects of two school-based PA intervention arms on educational variables and health markers in adolescents. This will provide valuable and innovative training to the educational community, enabling them to implement teaching methodologies that have the potential to enhance academic performance and improve the quality of life for their students.

**Clinical trial registration:**

clinicaltrials.gov, NCT05891054.

## Introduction

1

Physical activity (PA) in children and adolescents has not only been consistently associated with physical health (i.e., adiposity, cardiometabolic health, health-related physical fitness (HRPF), bone health, etc.) (1), but its impact extends to psychosocial health (i.e., well-being, self-image, anxiety, depression, life satisfaction, happiness, etc.) (2). Consequently, the World Health Organization recommends that children and adolescents aged 5 to 17 should accumulate at least 60 min of moderate-to-vigorous PA (MVPA) per day (3). However, there is a concerning scenario in Europe, where the majority of adolescents, exceeding 71%, fail to meet these PA guidelines (4). This lack of adherence to PA guidelines has significant implications for the development of non-communicable diseases.

Schools serve as environments where millions of children and adolescents, representing diverse socioeconomic backgrounds, cultures, and fitness profiles, coexist for extended periods of time. This makes the school an ideal setting for developing strategies to encourage the adoption of healthy lifestyle habits. Moreover, the American Heart Association recommends that children and adolescents should accumulate at least 30 min of MVPA in the school day (5). Nevertheless, a recent systematic review revealed that less than a quarter of children and adolescents worldwide meet these recommendations for PA during school hours (6). On average, children and adolescents accumulate only 3 to 22% and 2 to 8% of their school time in MVPA, respectively (6). Moreover, sedentary behaviors are prevalent during the school day, with children and adolescents spending a significant amount of time sitting at their desks (7, 8). Thus, the Sedentary Behavior Research Network recommends replacing screen-based learning activities with screen-free activities, preferably incorporating movement (9).

Currently, schools serve as alarming hubs of inactivity and sedentary behavior, necessitating strategies that aim to increase MVPA levels and reduce prolonged sedentary periods during the school day. Traditionally, physical education lessons and recess have been regarded as opportune periods to incorporate PA during the school day. However, such methods have proven ineffective in increasing PA levels, particularly among adolescents (10). As a result, there has been a growing interest in recent years in developing strategies to enhance PA levels during subjects traditionally taught in a static manner within the classroom, such as mathematics, geography, and history. Two such strategies are active breaks (AB) and physically active learning (PAL) (11, 12).

AB involve incorporating short breaks of PA (usually with moderate or vigorous intensity) into academic lessons, excluding physical education (13). Previous research has predominantly focused on the effects of AB on PA levels and educational outcomes. Notably, AB ranging from 5 to 15 min have been associated with improved PA levels during school hours (14–17). Regarding educational variables, the impact of AB on time-on-task has been investigated, and it appears to be significantly higher when AB are integrated (14, 16, 17). The results on other variables such as academic and cognitive performance are inconclusive (16, 17), likely due to the variability in measurement tools used across studies. It is important to note that most of the evidence on AB comes from studies conducted in primary education, and there is limited research on the effectiveness of this type of intervention in secondary education. Few studies that have evaluated the effectiveness of AB in secondary education have reported conflicting results regarding to the impact on time-on-task (18, 19). In relation to cognitive variables, it seems that AB of 4 min duration for 8 weeks is sufficient to significantly improve attention, concentration and mathematical calculation (20).

PAL involves integrating PA into lessons in key learning areas other than physical education (e.g., mathematics) (13). Previous studies have suggested positive effects of PAL on PA levels, time-on-task and academic performance in primary education children (21). However, there is no clear evidence regarding to the changes on HRPF, with some studies reporting significant effects (22, 23) while others do not (21). Likewise, as in AB, the effects of this type of intervention on cognitive markers are inconclusive (21). Once again, the available evidence in secondary education remains limited and inconclusive. PAL seems to be linked with enhancements in school-based PA levels, but not in overall PA (24). Moreover, there are contradictory findings regarding the impact of PAL on academic performance (25, 26). Additionally, there is a need for studies in this population that include other variables known to have a positive association with PA, such as time-on-task (27) and cognitive variables (28).

The scarcity of studies and the disparity of results found in secondary education, joined with the observed decline in PA levels during this stage (29, 30), underscore the importance of implementing interventions to promote and increase PA in the classroom. Moreover, if we focus on the Spanish context, to date no such interventions based on AB or PAL have been carried out in the secondary education classroom.

Thus, this study reports on the methods and rationale of the ACTIVE CLASS study. This randomized controlled trial (RCT) has two main objectives: (i) examines the effect of two active learning intervention (AB and PAL) on PA levels, sedentary time, educational indicators, cognition, and markers of physical and psychological health in secondary education students; (ii) evaluate teachers’ and students’ experiences about the implementation of these the two school-based PA intervention.

## Methods and analysis

2

### Study design

2.1

The ACTIVE CLASS study is a RCT, with randomization at school level [Clinicaltrials.gov (NCT05891054)]. An intervention is developed in two experimental groups (AB intervention and PAL intervention), with pre- and post-intervention measures. Additionally, a follow-up measure is conducted 4 weeks after the intervention to assess the sustainability of the intervention program.

ACTIVE CLASS is a multicenter study whose management is designed to ensure effective collaboration and communication between research groups. The research groups consist of qualified researchers and graduates in PA and sport sciences from two Universities (University of Cadiz and University of Extremadura, Spain). Both Research groups adhere to a common study protocol for training, fieldwork, data collection and management, and quality control procedures. There is continuous telematic contact during the development of the study. In addition, each research group has responsible investigators who manage the day-to-day running of the study in their centers and are in continuous contact with their counterparts at the other university to make decisions on aspects that require a quick response or do not require a meeting of all the in researchers.

### Participants and inclusion criteria

2.2

Participants in the ACTIVE CLASS study are apparently healthy adolescents from secondary schools in the provinces of Cadiz and Caceres (Spain). The schools included in the study are public secondary schools located in areas with a predominantly medium socioeconomic level (31). The ACTIVE CLASS study establishes the following inclusion criteria:

- *Participants’ inclusion criteria for adolescents’ students:* (i) studying 7th or 8th grade (12–14 years old); (ii) not having a physical disability or health problem that could limit PA levels.- *Schools’ inclusion criteria:* (i) having a minimum of 60 students in 7th and 8th grade; (ii) not participating in any other PA or health promotion program; (iii) Be located within a radius of 15 kilometers of the research group’s work centers in Cadiz and Caceres.

Figure 1 illustrates the flow diagram of the participants recruitment process. A total of 20 schools in Caceres and 64 schools in Cadiz are invited to participate through a letter of invitation addressed to the school’s management. A meeting is held with the management teams of the schools that accept the invitation, to explain the study and obtain their consent. From the total number of schools which accept to participate and provide their consent (three schools, both in Cadiz and Caceres), a randomization process at school level is conducted in each study province. Thus, three study groups are established in each city (Cadiz and Caceres): (i) AB intervention group, (ii) PAL intervention group, and (iii) control group. All students in the 7th or 8th grade of the participating schools who give their informed consent are invited to participate in the study. The parents of the students receive an information document describing the study, the inclusion criteria, the informed consent process, and an invitation to attend an information meeting at the school. To participate in the study, the parents or guardians must sign the informed consent form, along with the student’s consent.

**Figure 1 fig1:**
[figure not shown]
Follow diagram of study participants.

A total of 292 participants were included in the study, ensuring effect sizes of 0.1 with an alpha level of 0.05 and a power of 0.80, even with an experimental dropout rate of 25% (GPower 3.1.9.4, Düsseldorf, Germany).

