### Strengths and limitations

3.1

The present study has diverse strengths that should be mentioned: (i)the study is carried out on a sample of secondary education students. This is an educational stage which has received less attention in the scientific literature than primary and preschool education; (ii) the PAL intervention involves a collaborative approach between mathematics teachers and researchers, ensuring a higher level of sustainability of the intervention. This co-development process enhances the integration of PA into academic lessons and promotes long-term adoption by teachers; (iii) the study design will bring new evidence allowing to control the internal validity of the results. In addition, to corroborate the stability over time of the strategies offered, a follow-up measure of 4 weeks is incorporated at the end of the intervention.

On the other hand, some limitations should be mentioned: (i) the generalizability of the study results may be limited to the specific school context and characteristics of the participants included in the study (i.e., facilities, teachers, student motivation, etc.); (ii) the stability of the interventions may be compromised once the research team’s support is no longer available. Maintaining the AB and PAL interventions in real school settings without the continued support of the research team can be challenging.

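### The 80% power claimed for an effect of 0.1 with 292 students makes no allowance for randomising six schools, two per arm

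*Protocol article*

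**What the plan says.** The sample-size statement is one sentence in section 2.2, below Figure 1. It begins "A total of 292 participants were included in the study" and continues "ensuring effect sizes of 0.1 with an alpha level of 0.05 and a power of 0.80, even with an experimental dropout rate of 25"%, citing G*Power 3.1.9.4. It names no statistical test, effect-size metric, number of measurement waves or correlation between waves. It also names no ICC, design effect or number of schools.

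The unit of allocation is stated clearly elsewhere. Section 2.1 says "The ACTIVE CLASS study is a RCT, with randomization at school level". The Methods part of the abstract gives six schools, three in each of two provinces, and says "One school from each study provinces is randomly assigned to either the active break intervention group", with the other two arms filled in the same way. Section 2.2 repeats that allocation was done within each province. Each of the three arms therefore holds two schools, one per province.

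Section 2.5 plans repeated-measures models and says that the CONSORT guidance for cluster trials will be considered. Section 3.1 does not mention the number of schools among its limitations.

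**The concern.** Students in one school share teachers, timetable and surroundings, so their outcomes, and their changes in outcome, are usually correlated. When whole schools are allocated, that correlation inflates the variance of the arm comparison. The error term must also be estimated from very few units: six schools less three arms leaves three degrees of freedom per time contrast. A power figure built only from student numbers leaves out both effects.

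The stake is how the results are read. The sentence says that the trial ensures its stated power for an effect of 0.1. A reader who accepts this would take a non-significant result on physical activity or sedentary time as fair evidence against effects of that size. If the real power is well below 0.80, that inference is not available.

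**Working it through.** **Inputs from the protocol article.** N = 292, dropout 25%, effect size 0.1, alpha 0.05 and claimed power 0.80 (section 2.2). Six schools, k = 3 arms and m = 3 waves: before, after, and 4 weeks later (abstract, section 2.1).

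- Completers: 292 × 0.75 = 219.
- Completers per school: 219 / 6 = 36.5.

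**Assumptions, because the article is silent.** The metric is Cohen's f; the test is the group-by-time interaction; sphericity holds; the correlation between waves is ρ, with 0.5 as base case. The ICC of the tested change contrast is taken as 0.01, 0.02 and 0.05.

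**Step 1. The article's own figure.** With independent students, the noncentral F calculation uses

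λ = f² × N × m / (1 − ρ), df1 = (k − 1)(m − 1) = 4, df2 = (N − k)(m − 1).

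At N = 219 and ρ = 0.5: λ = 0.01 × 219 × 3 / 0.5 = 13.14 and df2 = 432, so power = 0.84. The N for 80% power is 204 with equal arms, or 204 / 0.75 = 272 with dropout. This is compatible with a claim of at least 0.80 at 292, but it is not an exact match. Power of exactly 0.80 at 219 needs ρ of about 0.456. With two waves, ρ of about 0.55 also gives 0.80. Two other readings fail even with independent students: a one-way comparison at f = 0.1 gives 0.24 at 219, and a pairwise standardised difference of 0.1 gives 0.10 at 292. The route is therefore plausible, not established.

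**Step 2. Design effect.** DE = 1 + (36.5 − 1) × ICC, and λ is divided by DE.

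**Step 3. School-level degrees of freedom.** The denominator df become (6 − 3) × 2 = 6, or (6 − 3 − 1) × 2 = 4 if province is also fitted.

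Results for ρ = 0.5:

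| ICC | DE | λ | Design effect only (df2 = 432) | df2 = 6 | df2 = 4 |
|---|---|---|---|---|---|
| 0 | 1.00 | 13.14 | 0.84 | 0.50 | 0.37 |
| 0.01 | 1.36 | 9.70 | 0.70 | 0.38 | 0.29 |
| 0.02 | 1.71 | 7.68 | 0.58 | 0.31 | 0.24 |
| 0.05 | 2.78 | 4.74 | 0.37 | 0.20 | 0.16 |

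On the design effect alone, power reaches 0.80 at an ICC of about 0.0025.

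**Step 4. Sensitivity to the correlation**, with df2 = 6:

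| ρ | ICC 0.01 | ICC 0.02 | ICC 0.05 |
|---|---|---|---|
| 0.3 | 0.28 | 0.23 | 0.15 |
| 0.5 | 0.38 | 0.31 | 0.20 |
| 0.7 | 0.59 | 0.48 | 0.31 |
| 0.8 | 0.77 | 0.67 | 0.45 |

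Every cell is below 0.80.

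**The case against.** The best defence has three parts.

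*The result depends on inputs that the article does not give.* This is true, and it limits what can be said. A reader might infer that the claim fails for any school-level correlation above zero. The calculations do not support that. With ρ = 0.7 and ICC 0.01, the design effect alone leaves power at 0.91. With ρ = 0.8 and ICC 0.001, power is 0.88 even with 6 df. A reader might also lift a single figure from the tables, such as power of 20 to 40%, or conclude that only very large effects are detectable. Such statements hold only under a chosen correlation, ICC and df, so none can be presented as a property of the trial.

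*Clustering is acknowledged.* Section 2.5 refers to the cluster extension of CONSORT, and the modelling detail may sit in an analysis plan that is not shown. This stands as far as the analysis goes: the article does not show that the final models will ignore schools, and that is not claimed here. It does not repair section 2.2, because a school-level analysis is exactly what lowers the power.

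*A journal article condenses.* An unprinted ICC would be no finding in itself. Here, however, the article prints a firm conclusion with its inputs, and those inputs describe students only.

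Two further inferences should be resisted. The sentence in section 3.1 that "the study design will bring new evidence allowing to control the internal validity of the results" makes no claim about power and is not evidence on this point. Arm and school are also not fully confounded: with two schools per arm, between-school variation can be estimated, though poorly.

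**Conclusion.** The power statement is wrong as written. It is a student-level figure attached to a trial that allocates six schools, and nothing in the article supports 80% power under that allocation. On the plausible route at correlation 0.5, the claimed 0.80 becomes 0.38, 0.31 and 0.20 for ICCs of 0.01, 0.02 and 0.05 with 6 school-level df, and 0.29, 0.24 and 0.16 with 4 df. Across correlations of 0.3 to 0.8 and those ICCs, power with 6 df runs from about 0.15 to 0.77. Among the cases run with 6 df, only a near-zero ICC together with a high correlation keeps it above 0.80.

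The direction of the error is firm. Its size is conditional on Cohen's f as the metric, the three-wave interaction test, sphericity, and the assumed correlation and ICC, none of which the article states.

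**What to change.** In section 2.2, either withdraw the 80% statement or replace it with a power or detectable-difference statement that allows for school-level randomisation. A replacement should give the test, the effect-size metric, the repeated-measures correlation, the assumed ICC range and the school-level degrees of freedom, including whether province is fitted. The resulting figures should be shown as a range and labelled as conditional on those assumptions.

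In section 3.1, add two schools per arm to the limitations.

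The cost is a short recalculation and rewording in two sections. No additional enrolment and no change to the conduct of the trial is needed. The downside is a less favourable stated figure.

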### Interventions

2.3

The ACTIVE CLASS study implements two intervention programs over a period of 16-weeks: (i) AB, and (ii) PAL, consisting of including PA in academic lessons for secondary education, while a third group serves as a control.

#### Active break intervention

2.3.1

AB intervention takes place daily and is carried out in the normal academic lessons, where two ABs per day are included in the 7th and 8th grade timetable of each secondary school. The timing of the AB is coordinated with the school management team. Whenever possible, one AB is scheduled before recess and the other after recess. It is important to note that no AB are scheduled during physical education classes or the lesson immediately following physical education. This ensures that the effect of the AB is not solely attributed to the PA performed in the preceding physical education class. The remaining class time follows the usual methodology without any variation.

The implementation of this intervention utilizes digital platform accessible to schools through individuals’ usernames and passwords. This platform has been specifically designed to facilitate the development of AB in school classes. An example of AB can be found in the following link: https://www.dropbox.com/s/dtye613hb3m3c50/VideoDescansoActivo.mp4?dl=0. This innovative tool allows to program different types of AB easily and quickly, by alternating variables such as physical exercise, its duration or intensity. Based on the findings from the review by Daly-Smith et al. (16), each AB has a duration of 5 min, of which 4 min of activity are used, including two sets of 20 s of work and 10 s of rest of four different exercises. Finally, a cool down consisting of deep breaths is performed. The activities selected for each of the AB include aerobic and strengthening activities (i.e., jumps, squats, lunges or skipping).

Teachers have access to the platform and are responsible for conducting the AB as scheduled by the research team. During the AB, students follow the instructions provided by an avatar that guides the session through the platform. To ensure the proper use of the platform, the research team provides training and support to the teachers. During the initial phase of the intervention, the research team accompanies the teachers for the first 2 weeks to ensure a smooth implementation of the AB and address any questions or concerns that may arise. This support aims to familiarize the teachers with the platform and ensure they feel confident in delivering the AB effectively.

#### Physically active learning intervention

2.3.2

PAL intervention involves integrating PA into academic lessons, specifically within the subject of mathematics. This subject has a substantial body of evidence supporting its applicability for PAL, as it is a core subject taught in all grades of secondary education (26, 32, 33). Out of the total number of mathematics lessons taught per week in Spanish schools (four one-hour classes per week), one class per week for 16 weeks is dedicated to the PAL intervention. Each of the PAL is developed outside the classroom during the intervention.

The mathematics teacher corresponding to this intervention group, previously trained and with the constant support of the research team, oversees implementing the strategies in their academic lessons. Before each PAL class, the research team and the mathematics teacher collaborate in a meeting to determine the specific content to be covered and co-develop the activities to be included in the session. Some examples of activities used in the sessions can be found in the following free downloadable book: https://www.dykinson.com/libros/aprendizaje-fisicamente-activo-fundamentos-teoricos-y-estrategias-practicas-para-la-materia-de-matematicas-en-1o-y-2o-de-eso/9788411701617/

